## Abstract

**Background:**

Given the high prevalence and cost of Alzheimer disease (AD), it is crucial to develop equitable interventions to address lifestyle factors associated with AD incidence (eg, depression). While lifestyle interventions show promise for reducing cognitive decline, culturally sensitive interventions are needed to ensure acceptability and engagement. Given the increased risk for AD and health care barriers among rural-residing older adults, tailoring interventions to align with rural culture and distinct needs is important to improve accessibility and adherence.

**Objective:**

This protocol aims to develop an intelligent recommendation system capable of identifying the optimal therapeutic music components to elicit engagement and resonate with diverse rural-residing older adults at risk for AD. Aim 1 is to develop culturally inclusive user personas for rural-residing older adults to understand their goals and challenges for music-based digital health intervention. Aim 2 is to develop knowledge embedding–based machine learning (ML) models that use music metadata and survey response data to identify optimal therapeutic music components for enhancing engagement and emotional resonance for depression among rural-residing older adults at risk for AD. Aim 3 is to assess acceptability for personalized therapeutic music sessions and ML-based music recommendations with a separate sample.

**Methods:**

Participants (N=1200) will be aged 55 years or older and residing in the United States. In phase 1, participants (n=1000) will receive 5 randomized songs and complete a survey to understand the sentiment, cultural relevance, and perceived benefit for each song. Brief, researcher-created Likert surveys will be used. In phase 2, survey data will be used to develop ML algorithms in collaboration with the University of Massachusetts Amherst Center for Data Science and Artificial Intelligence. These ML models will be integrated into the digital music intervention and tested with a separate sample of 200 participants. Similar to phase 1, participants will be provided with sets of songs generated by the recommendation system based on the target goal (ie, to reduce depression). The recommendation accuracy of the ML algorithm will be assessed using multiple performance metrics, including root-mean-square error and normalized discounted cumulative gain as well as the mean acceptability score with a goal of 85% user acceptability.

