**Figure 1 figure1:**
[figure not shown]
The SingFit mobile health app.

Due to the need for accessible and culturally relevant lifestyle interventions aimed at reducing AD risk, this protocol seeks to improve the cultural responsiveness of an existing digital music-based intervention, SingFit, aimed at improving depressed mood for individuals at risk for or experiencing AD. Much like digital health tools, cultural considerations are important for music-based interventions. Older adults from rural communities tend to prefer traditional genres of music such as country, folk, and gospel; are less likely to embrace newer music trends; and are often influenced by their family’s and community’s musical preferences [28,29]. The purpose of this study is to develop a machine learning (ML) recommendation system driven by the attitudes and cultural preferences of rural-residing adults. Since acceptability and engagement are important to the success of any health intervention, cultural considerations are at the forefront of this intervention design [30]. This is reflected by the study’s aims, which are as follows:

Develop culturally inclusive user personas for rural-residing older adults to understand their goals and challenges for music-based digital health intervention.Develop a knowledge embedding (KE)–based ML model that uses user data to identify optimal therapeutic music components for enhancing engagement and emotional resonance among rural-residing older adults at risk for AD.Assess the acceptability of personalized therapeutic music sessions and ML-based music recommendations in a digital music intervention.

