## Results

Participant recruitment for the final protocol was initiated on December 31, 2024. In June of 2025, participants had completed the phase 1 and 2 web-based survey studies (Figure 2). Data preprocessing and analysis is underway to prepare publication of the results.

Due to challenges with participant recruitment and high attrition related to the initial study protocol, the study team made 2 changes to the initial study design. All modifications were administratively reviewed by the external institutional review board and subsequently implemented in compliance with ethical guidelines. First, the initial eligibility criteria for participants included 2 or more risk factors for AD based on the Australian National University-Alzheimer’s Disease Risk Index (eg, education level). An amendment to the original study protocol was made to the “at least 2 risk factors” eligibility requirement. Additionally, due to the high attrition noted, the survey removed the need to download the SingFit app and moved all songs (.mp3 files) to Qualtrics. Multiple recruitment methods were planned, including word-of-mouth, crowdsourcing platforms (eg, Prolific), social media, and web-based caregiving organizations. However, once the above changes were made, recruitment was accomplished rapidly on a crowdsourcing platform (Prolific).

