### Limitations

A significant limitation of this work is that the music files were moved from the app and hosted in Qualtrics due to issues with recruitment and retention in phase 1. Participants were not exposed to the app user interface during the music preference surveys in phases 1 and 2, which may have altered the experience of the music intervention. However, only elements present in the app (ie, length of song play, liking songs, and music metadata) were used for building the ML models. Second, participants with cognitive impairment or AD were excluded. This may limit the generalization of the recommendation system and findings to cognitively health older adults. Lastly, the sample size of this pilot project was constrained by the 1-year funding period. Although 1000 participants represents a meaningful sample for a pilot study, it is relatively small for training KE models and may impact the model’s predictive performance for music recommendations. Future phases of this project will include additional training and refinement of the model using larger datasets to enhance the model’s performance and overall generalizability.

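### Aim 3 is worded as a test of the model integrated in the SingFit app, but phase 2 can only show acceptability of recommended playlists played in a web survey

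*Protocol article*

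**What the plan says.** Two places describe phase 2 as a test of the integrated product. The Abstract (Methods) says: "These ML models will be integrated into the digital music intervention and tested with a separate sample of 200 participants". The third aim in the Introduction reads: "Assess the acceptability of personalized therapeutic music sessions and ML-based music recommendations in a digital music intervention". The same part of the Introduction names the product to be improved as "an existing digital music-based intervention, SingFit", and the Figure 1 caption presents it as a mobile health app.

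Two other places describe what was run. In Results, "due to the high attrition noted, the survey removed the need to download the SingFit app and moved all songs (.mp3 files) to Qualtrics". In Discussion, Limitations: "Participants were not exposed to the app user interface during the music preference surveys in phases 1 and 2". The Limitations add that this is a change "which may have altered the experience of the music intervention", and answer it with the statement that "only elements present in the app (ie, length of song play, liking songs, and music metadata) were used for building the ML models".

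The Abstract (Objective) has a version of the aim that names no delivery platform: "Aim 3 is to assess acceptability for personalized therapeutic music sessions and ML-based music recommendations with a separate sample". Methods, Phase 2, says that users rate recommended playlists on the phase 1 survey. It defines the acceptability score as an average over liking, relevance and perceived benefit of those playlists, with 85% set equal to a mean of 4.25.

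**The concern.** The article gives two incompatible descriptions of the object being tested. In one it is a recommendation model working inside an existing app. In the other it is a list of recommended songs played as audio files within a questionnaire.

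This matters because Aim 3 carries the study's only acceptability criterion. If the mean passes 4.25, a reader of the Abstract and the aims will take it that the digital intervention, with the model built in, was found acceptable to its users. Nothing about installing, opening, navigating or returning to the app enters that result. The authors themselves allow that the interface is part of the experience, so the difference is not merely one of hosting.

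**Working it through.** This is a question of design and wording, so the check sets the statements side by side.

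1. **Object named in the claim.** Abstract (Methods) and Introduction aim 3: the model within the digital music intervention, which the Introduction identifies as SingFit.
2. **Object delivered.** Results: song files moved to Qualtrics, app download no longer needed. Limitations: no exposure to the app interface in phase 1 or phase 2. Of the 200 participants planned for phase 2, the number meeting the integrated app is therefore 0.
3. **Status of the two descriptions.** The Results and Limitations describe the design that was run. The Abstract and the Introduction aim are current text, not entries in a log of superseded wording. The clash is therefore inside the current document.
4. **What the score measures.** Methods, Phase 2, builds it from ratings of the playlists. It names no item on the app or its usability.
5. **What the criterion means.** The plan's own figure reproduces as 4.25 / 5 = 0.85. The 85% is a mean rating expressed as a fraction of the top of the scale. It is not the percentage of users who accept.
6. **Whether the stated mitigation closes the gap.** The Limitations reply that the model was built only from elements the app also has. That concerns the inputs to Aim 2. It says nothing about whether the Aim 3 ratings were given under app conditions.
7. **Whether sample size helps.** The minimum of 139 and the planned 200 govern how precisely the mean playlist rating is estimated. Neither changes what is being rated.

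Result: items 1 and 2 conflict. Items 4 and 5 agree with item 2 and with the platform-free aim in the Abstract (Objective). Items 6 and 7 do not remove the conflict.

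**The case against.** The best defence is that Aim 3 was always about songs. Both versions of the aim take sessions and recommendations as their object, and the Abstract (Objective) names no platform. The sentence after the one quoted from the Abstract (Methods) says participants receive sets of songs from the recommender, much as in phase 1. The score is defined on playlists. The Limitations put the missing app exposure first and call it significant. One could add that a digital music intervention is an elastic phrase that might cover songs in a web survey.

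Most of this stands. The playlist question can be answered and nothing is hidden. The last step fails, because the Introduction ties the phrase to SingFit and the Abstract speaks of integration followed by testing. A limitation in the Discussion does not correct that.

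Three stronger readings are tempting and are not supported:

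- **That Aim 3 cannot be answered at all.** It can, for recommended playlists.
- **That removing the app pushed the score upward.** The documents say only that the experience may have been altered. Losing the interface could lower ratings as well as raise them.
- **That early attrition is itself Aim 3 evidence, or that 85% should be multiplied by a retention rate.** The Limitations place the recruitment and retention problems in phase 1, where songs were chosen at random and no model recommendation was under test. The initial protocol also had a different eligibility rule, so the app's effect cannot be isolated. No attrition rate is given, and a mean of 4.25 out of 5 is not a share of users that could be multiplied by retention.

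**Conclusion.** The concern holds in a limited form. The Abstract (Methods) and the third aim in the Introduction attribute to phase 2 a property it did not have, namely a test of the model inside the app. A favourable Aim 3 result would support acceptability of recommended playlists heard in a Qualtrics survey, and no more.

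The effect is on the permissible conclusion, not on any number. The 4.25 threshold, the sample sizes and the analysis are untouched by this point. The verdict assumes that the Limitations statement about phases 1 and 2 applies to every phase 2 participant, as it is written, and that the digital music intervention in the aim is SingFit, as the Introduction indicates.

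**What to change.** Make three wording changes before the results are reported:

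- **Abstract (Methods):** replace integration and testing in the intervention with testing of the model's recommended playlists, delivered as audio in a web survey.
- **Introduction, aim 3:** align it with the platform-free version in the Abstract (Objective), and name the web survey as the setting.
- **Methods, Phase 2, Aim 3 criterion:** state that the 85% goal (mean 4.25) refers to acceptability of recommended playlists in that setting.

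Add one sentence, in the Limitations and wherever the Aim 3 result is stated, that acceptability of the app with the model integrated was not tested.

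If counts from the initial app-based version are available, which the article does not say, report them descriptively as context. Keep them out of the Aim 3 score and note that eligibility and song content differed.

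The cost is a few sentences and a narrower claim. No new data are needed. Keeping the wider claim would require a further sample using the model in the app, since recruitment for both phases is complete.

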**Results:**

Participant recruitment is complete for phases 1 and 2 as of June 2025. Data analysis for the results of aims 1, 2, and 3 are underway and results are expected to be published in the fall of 2025.

**Conclusions:**

This protocol seeks to use ML to improve the equitability and accessibility of a digital lifestyle intervention for AD.

**International Registered Report Identifier (IRRID):**

DERR1-10.2196/73711

## Introduction

The prevalence of Alzheimer disease (AD) is expected to increase from 55 million cases worldwide in 2021 to an estimated 78 million cases by 2030 [1]. In 2024, the estimated health care cost of AD in the United States was $360 billion [2]. By 2050, it is estimated that the total annual health care cost will be $140,012 per US individual with AD, adding up to a total annual cost of $1.5 trillion [3]. Given the rising societal impact of AD, there is an urgent need for more preventative interventions.

One such preventative intervention is a lifestyle-based approach focusing on addressing modifiable risk factors of AD, such as smoking, diet, and depression [4]. Research investigating lifestyle interventions has yielded promising results [5,6]. The Finnish Geriatric Intervention Study to Prevent Cognitive Impairment and Disability randomized controlled trial examined a 2-year multidomain intervention for adults aged 60 years or older aimed at nutrition, physical activity, cognitive training, social support, and vascular risk factors [5]. The trial intervention showed beneficial changes in cognition and risk of cognitive decline and demonstrates the promise of lifestyle interventions for reducing the risk of overall cognitive decline (control group odds ratio=1.31; intervention group odds ratio=1) [5]. Research has also shown that treating depression can significantly reduce the risk of dementia [7]. Lifestyle-based approaches hold promise for preventing AD when designed to be accessible, especially for those at high risk of developing AD.

Older adults in rural communities face unique health challenges that place them at an even greater risk for AD. Social determinants of health, such as health care access and social engagement, coupled with psychosocial barriers (eg, stigma and medical mistrust) often exacerbate their risk [8,9]. These individuals face greater barriers to accessing lifestyle interventions, including limited health care resources, unreliable transportation, and reduced access to psychosocial support [10]. However, the majority of rural residents have access to broadband internet services [11], meaning digital lifestyle interventions may offer a more feasible, accessible, and cost-effective way to mitigate AD risk compared to traditional methods [12].

Although emerging research highlights the promising utility of lifestyle interventions, there remains a critical need for culturally sensitive approaches. Rural communities are often underrepresented in the development of digital cognitive and mental health tools, despite being disproportionately affected by cognitive and mental risk factors [13]. Research shows that interventions designed to be culturally sensitive can result in higher adherence and engagement with the intervention [14,15]. Additionally, intentional and meaningful inclusion of rural perspectives during the development of digital health interventions ensures individuals from rural, underrepresented communities actively participate in shaping their cognitive health landscape. Given the potential benefits of lifestyle interventions, culturally engaging and accessible interventions are needed to ensure utility and adherence.

One digital music intervention, SingFit, was developed to improve well-being and mood symptoms for both those at risk for and those living with AD (Figure 1). The use of singing to manage symptoms of depression is based on research showing that music interventions and music learning are associated with improvements in cognitive reserve, well-being, and mood symptoms related to depression [16-19]. A network meta-analysis found evidence supporting the use of music therapy or music listening ≥60 minutes a week for improving depression in persons aged 60 years and older [20]. Furthermore, research has shown that music-based interventions reduce anxiety, agitation, and other neuropsychiatric symptoms associated with AD [21-23]. SingFit encourages active engagement in music-making by providing an auditory lyric prompter before each sung phrase. It uses music associated with each user’s reminiscence bump, which is the tendency for older adults to recall more personal memories associated with adolescence and young adulthood [24,25]. The app follows music therapy guidelines and clinical practice, where familiar, preferred music is often used to promote relaxation and positive affect [26]. This music is specifically chosen to elicit engagement, long term memory, and narrative speech. This intervention is further described in Brown and Myers [27].

**Figure 1 figure1:**
[figure not shown]
The SingFit mobile health app.

Due to the need for accessible and culturally relevant lifestyle interventions aimed at reducing AD risk, this protocol seeks to improve the cultural responsiveness of an existing digital music-based intervention, SingFit, aimed at improving depressed mood for individuals at risk for or experiencing AD. Much like digital health tools, cultural considerations are important for music-based interventions. Older adults from rural communities tend to prefer traditional genres of music such as country, folk, and gospel; are less likely to embrace newer music trends; and are often influenced by their family’s and community’s musical preferences [28,29]. The purpose of this study is to develop a machine learning (ML) recommendation system driven by the attitudes and cultural preferences of rural-residing adults. Since acceptability and engagement are important to the success of any health intervention, cultural considerations are at the forefront of this intervention design [30]. This is reflected by the study’s aims, which are as follows:

Develop culturally inclusive user personas for rural-residing older adults to understand their goals and challenges for music-based digital health intervention.Develop a knowledge embedding (KE)–based ML model that uses user data to identify optimal therapeutic music components for enhancing engagement and emotional resonance among rural-residing older adults at risk for AD.Assess the acceptability of personalized therapeutic music sessions and ML-based music recommendations in a digital music intervention.

## Methods

### Participants

This survey study will lay the foundation for developing ML algorithms for an accessible music intervention for rural-residing older adults who are at risk for AD. Twelve hundred participants will be enrolled in the study. Eligibility for this study includes participants aged 55 years or older who have possession of a smartphone and the ability to read and understand English. Participants with self-reported presence of a diagnosed psychiatric or neurological condition, including AD, will be excluded. Recruitment was facilitated using a crowdsourcing research platform, Prolific.

### Ethical Considerations

The Salus Institutional Review Board determined that the present study was exempt in accord with 45 CFR 46.104(d)(2i, 2ii, 3A & 3B) on June 17, 2024. The exemptions fall under benign behavioral interventions or educational surveys where disclosure of responses would not result in risk of harm or civil liability, and where the information being recorded is anonymous or cannot be readily ascertained or linked to participants. Broad informed consent was obtained via an introductory paragraph on the survey, where participants were directed to continue with the survey to indicate acceptance. Participants were provided information on opting out of the study by emailing the principal investigator. Obtaining a signed informed consent would identify participants’ names, thus increasing the risk of linking information back to individuals. All participant data collected through Prolific was anonymized by the platform’s design. Prolific assigns participants a unique alphanumeric ID that is not linked to any personally identifying information. Researchers do not have access to names, email addresses, IP addresses, or any direct identifiers. Participants are paid $8 total for their participation in this study to complete the 45-minute survey. The CHERRIES (Checklist for Reporting Results of Internet E-Surveys) guidelines were used to guide the reporting of this protocol [31].

### Phase 1: Data Collection and Preprocessing

In phase 1, web-based survey data will be collected from up to 1000 older adults. Participants will be instructed to sing along to a playlist designed to reduce mood symptoms associated with depression. This goal was selected because depression is known to significantly increase the likelihood of AD and accelerate cognitive decline [32]. Participants will receive 5 songs randomly chosen from a set of songs based on age and musical arousal—2 factors known to be associated with mood and relevance to older adults. Songs will be selected based on participants’ “reminiscence bump” [24] and will use the iso principle to modulate from low arousal to moderate arousal [33,34]. In past studies of the musical “reminiscence bump,” the strongest associations and familiarity with music was found to be between the ages of 15-24 years [25,35]. SingFit’s music selections are chosen from participants’ adolescence and young adulthood to ensure familiarity and narrative memory associations with the music. The iso principle gradually shifts the music from matching the participant’s emotional state (eg, sad) to their desired state (eg, calm). In phase 1, songs with high arousal were not included in order to modulate arousal and affect gradually for a depression playlist in keeping with the iso principle. Surveys will use 5-point Likert scales to measure song familiarity, perceived benefit, sentiment, relevance, and preference for each song, which will be analyzed in conjunction with music metadata (described below) to better understand musical factors associated with mood symptoms of depression. Participants will receive an open survey link to the Qualtrics survey and either listen or sing along to each song while completing survey questions for each song (ie, song preference or sentiment).

For the development of user personas and the ML model (aims 1 and 2), the planned sample size of 1000 participants was determined following deliberation with the study’s data consultants to balance feasibility and analytical utility within the scope of this pilot project. This sample was identified as the minimum viable cohort necessary to support adequate model training, validation, and initial testing of the recommender system.

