### Measures

Measures for this study are brief researcher-created surveys to measure song preference, expectation, and helpfulness for each song (see Multimedia Appendix 1). These measures were chosen to understand user preference in order to build a KE ML model and user personas for aims 1 and 2. These same measures will again be collected in a smaller sample for aim 3 to assess the acceptability of the ML-based music recommendations. Web-based surveys were developed by [name] and tested for usability and technical functionality by [name] and [name] prior to participant recruitment. Participants will be asked to answer each question for each song. Questions are 5-point Likert scales to measure song preference (strongly dislike to strongly like), sentiment (very sad to very happy), expectation for hearing that particular song for the goal of reducing depression (strongly disagree to strongly agree), and helpfulness (eg, “Would this song be helpful in making you feel better if you were very sad?”; strongly disagree to strongly agree). Participants will also be asked to assess their mood (eg, “How depressed are you?”) and engagement in daily activities prior to and directly following their survey on an 11-point Likert scale (0-10). Participant demographics will also be collected excluding directly identifying information that would link survey responses to participants.

Zip codes will be collected to verify geographical residence (rural, urban, or suburban) in order to build specific user personas tailored to each group (aim 1). After verification, only the first 3 digits of the zip code will be stored for each participant, and the digits will be changed to 000 in instances for which the zip codes contain less than 20,000 people.

Bot detection for survey entries based on reCAPTCHA was used, and any duplicate survey entries based on Prolific IDs were removed. Prolific uses participants’ email address and phone number to verify participants and IP address detection to ensure participants do not participate in studies more than once. There were an average number of 6.5 items per page with 8 total pages. All questions required an answer in order to submit the survey. Demographic questions included a “none of the above” or “prefer not to say” option, while music preference questions required a response on a 5-point Likert scale.

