### Music Metadata

Each song in the SingFit catalog has been tagged with metadata for dozens of different parameters. Musical metadata include linguistic syntax and semantics (assessed with text analysis software), tempo and key (assessed using song analyzer software), genre, popularity, arousal, and others. The full list of metadata is proprietary to Musical Health Technologies but encompasses a wide range of cognitive and affective factors associated with known therapeutic benefits. These metadata will be used to understand the musical factors associated with user preference and clinical factors related to improvement in depressed mood. Music metadata is used in SingFit’s current song recommendation algorithms and will be used in knowledge graphs for comparing various KE model architectures during phase 1.

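### In phase 1, arousal and features that track it are confounded with song position, and the model inputs described do not include position

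*Protocol article*

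**What the plan says.** The Phase 1 section of the protocol article describes the random element as a draw of songs: "Participants will receive 5 songs randomly chosen from a set of songs based on age and musical arousal". The Abstract's Methods paragraph says that "participants (n=1000) will receive 5 randomized songs". Neither sentence says that the order of presentation is random. The same Phase 1 section gives a direction to the sequence: songs "will use the iso principle to modulate from low arousal to moderate arousal", and "songs with high arousal were not included in order to modulate arousal and affect gradually".

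Ratings are collected along that sequence. Participants "either listen or sing along to each song while completing survey questions for each song". Mood is recorded only "prior to and directly following their survey on an 11-point Likert scale", so it belongs to the whole session and not to a song. The Ethical Considerations section says that participants "complete the 45-minute survey".

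The Music Metadata section lists arousal and tempo among the song features and gives them an interpretive role: "These metadata will be used to understand the musical factors associated with user preference and clinical factors related to improvement in depressed mood". Aim 2 is to find which musical components work best. The Limitations section lists what went into the models: length of play, liking of songs, and music metadata. Song position is not on that list.

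**The concern.** If arousal rises from the first song to the last for everyone, a low-arousal song is nearly always an early song and a moderate-arousal song a late one. A rating that changes with position for any non-musical reason then looks like a response to arousal. Carry-over is part of the plan's own rationale, since the order is meant to move the listener's state gradually. If it succeeds, later songs are rated in a different state from earlier ones. Tiredness in a long survey may add to this.

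The planned evaluation would not reveal the problem. Cross-validation splits by user, but training and test users hear the same kind of ordering, so the test folds carry the same drift. A model that learns the drift through arousal could gain NDCG over the purely random recommender without any musical effect.

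At stake is the interpretive half of Aim 2: what is said about arousal, and any weight the recommender gives to it.

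**Working it through.** The protocol states no figure on this point, so there is none to reproduce. The question is what the described design can identify.

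**Inputs from the protocol.** 1000 participants, 5 songs each, low-to-moderate order, ratings per song.

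**Assumed inputs, not in the protocol.** Drift of -0.1 rating points per position; between-person SD 0.7; within-person SD 0.97; arousal coded 0 (low) to 1 (moderate); true arousal effect 0. The arousal scale and the number of low and moderate songs are not given, so several patterns were tried.

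**Bias by hand.** With a drift of b per position and no position term:
- First-to-last contrast: 4 steps × b. For b of 0.05 to 0.10 in size, 4 × 0.05 = 0.2 and 4 × 0.10 = 0.4.
- Two low then three moderate songs: b × (mean position of moderate songs − mean position of low songs) = -0.1 × (4 − 1.5) = -0.25.
- Three low then two moderate songs: -0.1 × (4.5 − 2) = -0.25.

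**Simulation** (within-person least squares, 200 replicates, plus an unrelated two-level feature standing in for genre, drawn at random at each position):

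| Arousal over positions 1 to 5 | Correlation with position | Apparent arousal effect, no position term | With linear position term (SE) | Free position effects |
|---|---|---|---|---|
| Five equal steps | 1.00 | -0.40 | not estimable | not identified |
| Two low, three moderate | 0.87 | -0.25 | 0.01 (0.058) | not identified |
| Three low, two moderate | 0.87 | -0.25 | 0.00 (0.058) | not identified |
| Graded, song-level SD 0.1 | 0.97 | -0.40 | 0.02 (0.18) | identified |
| Graded, song-level SD 0.2 | 0.90 | -0.38 | 0.01 (0.10) | identified |
| Two low, three moderate, order randomised | 0.00 | 0.00 | 0.00 (0.028) | identified |

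Three things follow.
1. Without a position term, every rising pattern turns pure drift into an apparent arousal effect.
2. With a position term, the answer depends on how much arousal varies among songs at the same position. If it does not vary, a two-level pattern can be rescued only by assuming that drift is linear, with twice the SE of a random order (0.058 against 0.028). Five equal steps cannot be rescued at all.
3. The genre-like feature is unbiased even without a position term: its estimates lie between -0.002 and 0.004.

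**The case against.** A reader might infer that Aim 2 cannot separate any musical effect from order. The protocol does not support that. Songs are drawn at random within the age and arousal set, so genre, key or lyric content can differ at the same position and can be compared there. Nor is the confounding of arousal necessarily complete: it is total only if arousal is a fixed function of position, and the article does not say how closely the two are tied. That every playlist follows the rising order is also an inference, from one described ordering with no stated exception.

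A reader might also infer that Aim 3 is biased. It is not, in this respect. Aim 3 compares mean acceptability with a fixed value of 4.25 in a separate sample. A badly weighted arousal feature could make recommendations poorer, but would not create a false success. The 0.2 margin and SD of 1.2 quoted for Aim 3 are no yardstick for a phase 1 contrast.

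On NDCG, the metadata-only baseline uses the same ratings and could exploit the same drift. Distortion of the comparison between the embedding model and that baseline is therefore not shown.

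Finally, one can say that a condensed article need not list a position term, and that the feature set is still to be explored. This has some weight, but the exploration described concerns metadata features, and the Limitations section does list the inputs used, without position. The ordering is also stated in the article and is not a detail left out.

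What stands from all this: the point is limited to arousal and its correlates, and its size is unknown.

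**Conclusion.** The point holds in a limited form. As described, phase 1 ties arousal, and any feature that tracks it, to song position, and the stated model inputs offer no way to tell them apart. Whether tempo is affected depends on how closely it follows arousal in this catalogue, which the protocol does not say.

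The bias is proportional to an order effect that the protocol does not give: 0.2 to 0.4 points from first to last song under an assumed drift of 0.05 to 0.10 per position, and zero if there is no drift. The conclusion assumes that songs were presented in the order the iso principle implies. If the survey in fact randomised the order, the concern falls away and a sentence saying so would settle it.

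For prediction alone the confounding matters less. It matters for the stated purpose of understanding which musical factors relate to preference. Correcting it is a cheap improvement and worth making before Aim 2 is reported.

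**What to change.** Recruitment is complete, so order can no longer be randomised in phase 1. The analysis can still be changed:

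1. Take each song's position (1 to 5) from the survey layout and state how songs were ordered.
2. Adjust the per-song ratings for position before or while fitting the models and the metadata-only baseline. Position belongs to a user-song rating and not to a node of the graph, so adjusting the ratings before the graph is built is probably the simplest route. Estimate the adjustment in the training folds only.
3. Report how much arousal varies among songs at the same position, and estimate arousal-related effects from that variation.
4. Report NDCG with and without the position adjustment.
5. If arousal hardly varies within position, state that its effect cannot be separated from order, and leave arousal out of the conclusion about which musical components are best.

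The cost is one variable that should already be known, a short addition to the analysis text and a second NDCG run. The statistical price is lower precision for arousal-related effects, and possibly the loss of some true arousal signal that lies between positions.
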